### Procedure

The procedures in the current study have been approved by the ethics board of Ruhr University Bochum (176268). During participant recruitment and treatment, two study centers (Hamm and Hamburg; Hamm is the coordinating center) will provide a mindfulness-based group intervention in addition to what is routinely provided as standard inpatient SUD treatment. Patients admitted to either study center because of SUD treatment and who have completed detoxification are given information about the study and their possible participation if they are eligible for study participation according to the inclusion and exclusion criteria. After written informed consent is given by both the patient and their parent or guardian, the *t*_0_ assessment will be performed within 1 week after the transition from detoxification treatment to after-detoxification treatment. After the *t*_0_ assessment, patients will be randomized to either the intervention group (mindfulness-based group intervention in addition to standard treatment) or the control group (standard treatment as usual). The patients will be randomly allocated to either the Mind It! group or the control group in a 1:1 allocation ratio, stratified by study center with variable block lengths. The randomization lists will be prepared by the Department of Medical Biometry and Epidemiology of the University Medical Center Hamburg-Eppendorf. The central allocation procedure is managed by the coordinating study center in Hamm to guarantee allocation concealment.

The intervention group receives a mindfulness-based group intervention consisting of 12 45-min sessions relating mindfulness techniques to substance use problems in adolescents. In each of the first 4 weeks of the intervention, the participants receive two 45-min sessions of the core mindfulness-based group intervention. At the end of the 4 weeks, they undergo the first interim assessment (*t*_1_). In weeks 5–8 of treatment, intervention group participants receive one weekly 45-min session of the sustained mindfulness-based group intervention (maximum of four sessions). After the total mindfulness-based group intervention and after 8 weeks of treatment, participants undergo another assessment (*t*_2_), which is followed by the final assessment (*t*_3_) 6 months after *t*_2_. Assessments for *t*_3_ are performed by study personnel and participants receive €50 and travel expenses as compensation for participation in the *t*_3_ assessment. The mindfulness-based group intervention is delivered by clinically experienced researchers, who are currently in therapeutic training or have finalized therapeutic training, and are experienced in giving mindfulness-based interventions. Figure 2 gives an overview of the study flow.

**Fig. 2 Fig2:**
[figure not shown]
Schedule of enrolment, interventions, and assessment for the Mind it! trial. CCS-7 cannabis craving screening, DERS Difficulties in Emotion Regulation Scale, ENACT Enhancing Assessment of Common Therapeutic Factors, GAF Global Assessment of Functioning, GTS-P Gruppentherapiestundenbogen, HEISA Heidelberg scale for abstinence confidence, H-FERST Heidelberger Fragebogen zur Erfassung von Emotionsregulationsstrategien, MAAS-A Mindful Attention Awareness Scale for Adolescents, MBRP-AC Mindfulness Based Relapse Prevention Adherence and Competence Scale, MTASA Mindfulness Thinking and Action Scale for Adolescents, PSS-4 Perceived Stress Scale, SAFE Structured Assessment of Feasibility, SDS Severity of Dependence Scale, TLFB Timeline Followback, UPPS impulsive behavior scale

### Standard SUD treatment

In both study centers (Hamm and Hamburg), the standard SUD treatment has two structured, multidimensional treatment phases: (1) During the detoxification phase of treatment, the protected environment guarantees safe detoxification and constant monitoring of possible withdrawal symptoms. Within that setting, detailed psychiatric, neuropsychological, and psychosocial diagnostic assessments are performed. First psycho-education elements are used to address patients’ background SUD problems. Moreover, patients are motivated to continue treatment after detoxification. (2) Treatment after the detoxification phase addresses comorbid problems and disorders as the background of their SUD. Psycho-educational interventions are used to motivate patients to abstain from substance use in their future life and they are taught useful skills (e.g., against relapse). The SUD treatment integrates psychotherapeutic, somatic, and medical interventions with kinesiatrics, family therapy, occupational and educational therapy, and music therapy. These treatment elements are delivered in individual or group sessions.

### Intervention group

The mindfulness-based group intervention under evaluation in this study will be written up as a manual and is based on previous studies on MBCT [26, 41], MBCT for children [42], and MBRP [26–30, 41]. Research has indicated that MBRP can significantly reduce the risk of craving-induced relapses in SUD patients. The current manual will be closely aligned to the existing English-language treatment manual by Himelstein and Saul [43], *Mindfulness-based substance abuse treatment for adolescents*, which was developed in California for incarcerated youth with SUD problems but was later validated in inpatient, outpatient, educational, and community settings as a group intervention [35, 43–45].

The mindfulness-based group intervention integrates both formal mindfulness meditation practices from MBCT (such as body scan meditation, mindfulness of the breath meditation, mindfulness of the body in movement, and sitting meditation) and informal mindfulness practices, which supports participants to integrate mindful awareness into their daily routines. Inquiry is used as a group technique to reflect on experiences during meditation and psycho-education elements are used to teach participants about substance use, stress, stress reactivity, cravings, and coping skills, and they are given a rationale on why mindfulness helps with substance use problems. Each session includes formal mindfulness meditation practice and participants are encouraged to practice mindfulness outside the group sessions.

The group intervention mindfulness practice is adapted to the developmental needs of the young participants regarding duration and content. Therefore, we decided to make group sessions rather short (45 min) but deliver them more often compared with mindfulness-based intervention sessions with adults, such as, for example, MBCT or MBRP. Group sizes will be limited to a maximum of eight participants, so that individual attention can be given to them. Moreover, we plan to integrate simple sensory exercises, movement exercises, and playful activities with significant variation in the mindfulness practice rather than delivering an extended talk. Sessions will include SUD-specific treatment elements from MBRP (such as the identification of possible relapse triggers), mindfulness-based coping skills (such as acceptance), and skills specifically targeting cravings (such as urge surfing) [30].

The first eight sessions of the intervention (the core intervention) focus on delivering this content. The final four sessions (the sustained intervention) extend on this in that the participants are strongly encouraged to practice meditation and mindfulness every day using audio material and written intervention material and to record their practice on diary cards.

### Primary outcome

Participants’ substance use will be assessed using the standardized, calendar-based Timeline Followback (TLFB) interview format [46]. In this interview, we will use paper-based screening questions on lifetime use of nicotine, alcohol, cannabis, opioids, cocaine/ crack, designer drugs, methamphetamine, amphetamine, unprescribed medication, and other drugs so that we can target only those substances that each patient has used. The TLFB interviews will also focus on substance use within the past 30 days prior to detoxification and assessment (*t*_0_). The primary outcome of the study is the number of days with substance use within the past 30 days 6 months after the end of the intervention (*t*_3_) [32, 47].

### Secondary outcomes and mediating variables

Secondary outcomes include: (a) measures associated with SUD symptoms such as cravings, severity of dependence, relapses, and abstinence motivation, (b) measures of comorbid symptoms and overall functioning, such as general level of functioning, number of disability days (clinical standard), current medication (clinical standard), sexual risks, and health-related quality of life, (c) participant satisfaction with the mindfulness-based group intervention (intervention group only), and (d) proximal measures relating to intervention content such as mindfulness, mindfulness practice, perceived stress, emotion regulation, and impulsivity. For this last category of secondary outcomes (d), we also seek to explore whether changes in these measures possibly mediate the effects of the mindfulness-based group intervention on SUD symptoms, such as cravings or substance use.

#### Cravings

The inventory for an assessment of cannabis cravings (CCS-7) [48] is a validated German seven-item version of the English language Marijuana Craving Questionnaire [49]. The CCS-7 comprises two dimensions of cravings: relief cravings (e.g., “If I were smoking marijuana right now, I would feel less nervous”) and reward cravings (e.g., “It would be great smoking marijuana right now”), with Cronbach’s alpha ranging from .78 to .85. For participants who do not identify cannabis as a problem substance, we provide visual analogue scales to measure their current cravings for problem substances.

#### Severity of dependence

The Severity of Dependence Scale (SDS) [50] was developed to assess the psychological components of substance dependence symptoms. It comprises five items and focuses on symptoms of loss of control and distress with regards to substance use (e.g., “Did you think your use of … was out of control?”). This scale has good validity and internal consistency (Cronbach’s alpha ranging from .81 to .90).

#### Abstinence motivation

The Heidelberg scale for abstinence confidence (HEISA) [51] is a German self-report measure that assesses patients’ confidence in whether they can abstain from substance use in different situations. The introductory item of this scale assesses patient’s goal with regards to their future substance use, asking respondents to choose their substance use goals ranging from “remain totally ‘clean’ – never use substances again” to “use substances as before.” We use this single introductory item to assess each participant’s abstinence motivation .

#### Comorbidity

Comorbid disorders will be assessed through clinical interviewing and the DISYPS-III diagnosis checklists on symptoms of attention deficit and hyperactivity disorder, conduct disorder, depression, anxiety, and trauma [52]. The checklists are used to diagnose disorders within these symptom spectra according to ICD-10 and DSM-V.

#### General level of functioning

We will use the ICD-10 Global Assessment of Functioning (GAF) to assess participants’ social and psychological functioning on a numeric scale (1 = persistent danger to 100 = no symptoms). The assessment will be carried out by clinicians or trained study personnel.

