### Measurement

Participants are asked questions in structured clinical interviews and they complete questionnaires. Their hands are scanned so that we can calculate the 2D:4D ratio (*t*_0_ only), and they undergo a computerized assessment for several neuropsychological tasks at four points within the study process: after detoxification and before randomization and the following SUD treatment phase (*t*_0_), 4 weeks into treatment (*t*_1_), 8 weeks after *t*_0_ (*t*_2_), and 6 months after *t*_2_ (*t*_3_). Figure 1 gives an overview of the measures used.

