### Methods against bias

The study follows the CONSORT statement for randomized controlled trials [40]. This includes the publication of a study protocol and the study’s public registration (German Register of Clinical Studies, DRKS00014041). The procedures for study inclusion and assessment (obtaining informed consent, handling of questionnaires, clinical records, and clinical interviews) are performed by study personnel who remain blind to the participants’ randomization to either the intervention group (mindfulness-based group intervention “Mind it!”) or the control group (treatment as usual) and who are not involved in providing treatment. Blinding of patients is not possible due to their (non-)participation in the mindfulness-based group intervention. Self-reports regarding substance use are validated through urinalyses, which are routinely taken as part of SUD treatment and are extracted from medical records. Diagnostic assessments are based on highly standardized measurement tools and clinical information is provided by experienced clinicians. All study personnel are trained to conform to current guidelines and regulations (e.g., data safety). Questionnaire data will be computerized by trained staff using the EpiData software to ensure the high quality of the entered data. Additionally, a clinical research organization will monitor adherence to the study protocol and overall study quality. A data and safety monitoring board will oversee study procedures, recruitment, and data flow twice yearly and advise project staff when necessary.

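### The rule on who rates the GAF admits clinicians who are not required to be blind, which is inconsistent with the article's statement on blinded assessment (minor)

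*Protocol article*

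**What the plan says.** Three places in the protocol article bear on who rates and when, and a fourth fixes the baseline.

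- **Methods against bias.** Inclusion and assessment procedures, with clinical interviews named among them, "are performed by study personnel who remain blind to the" allocation "and who are not involved in providing treatment". The same section adds that "clinical information is provided by experienced clinicians", without saying whether those clinicians are blind. On patients it is explicit: "Blinding of patients is not possible due to their (non-)participation in the mindfulness-based group intervention".
- **General level of functioning.** The GAF is a numeric rating from 1 to 100 of social and psychological functioning. On the rater: "The assessment will be carried out by clinicians or trained study personnel".
- **Procedure.** The t3 assessments "are performed by study personnel and participants receive €50" as compensation.
- **Measurement.** The t0 assessment takes place "after detoxification and before randomization and the following SUD treatment phase".

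The section on secondary outcomes lists general level of functioning in group (b), and Analyses makes all secondary outcomes exploratory. The caption of Fig. 2 includes the GAF among its abbreviations, but the schedule itself is not shown in the text available, so the visits at which the GAF is rated cannot be read off.

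**The concern.** The safeguard and the rater rule do not fit together. In the GAF sentence, the word joining the two groups makes clinicians an alternative to study personnel, so the blinding statement, which is about study personnel, does not reach them. No other sentence says that they are blind or independent of treatment.

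This matters because the GAF is an observer's judgement, whereas most other scales in the article are self-reports. A rater who knows the allocation can let that knowledge into the score. A reader of Methods against bias would nevertheless take a reported GAF difference as coming from blinded raters. At stake is the interpretation of one exploratory secondary outcome during the treatment phase.

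**Working it through.** The article gives no figure on rater bias, so the check is mainly a reading of the sections side by side.

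**1. Are the clinicians covered by the blinding statement?** No. It is confined to study personnel. The Sample section draws the same line: treating clinicians make the diagnosis and study personnel verify it. That usage suggests, but does not prove, that the GAF clinicians belong to the treating team.

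**2. Could such a clinician learn the allocation?** Readily, if part of the treating team. Patients are not blinded. Under Procedure, intervention patients attend two sessions a week for four weeks and then one a week for up to four weeks, during inpatient or day treatment. Groups have at most eight members (Intervention group).

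**3. Which visits are exposed?**

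| Visit | Relevant statement | Exposed to knowledge of allocation? |
|---|---|---|
| t0 | Before randomization | No |
| t1 (4 weeks) | Only the general GAF rule applies | Yes, if the GAF is rated then and by a clinician |
| t2 (8 weeks) | Only the general GAF rule applies | Yes, on the same conditions |
| t3 (6 months after t2) | Study personnel, described elsewhere as blind | No, as assigned |

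**4. What does a change of rater type between t2 and t3 do?** Write the expected GAF in arm a at visit v as μ(a,v) + r(v), where r(v) is a rater effect common to both arms. The between-arm difference at visit v is then μ(1,v) − μ(0,v), because r(v) cancels. It therefore also cancels in the change of that difference between visits, which is the group-by-time term. Only a shift that depends on arm survives. If a share q of ratings comes from unblinded clinicians who shift intervention patients by δ standard deviations relative to controls, the bias at that visit is b = q × δ.

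**5. Illustration of what b could do.** The number per arm is taken from Sample size calculation. The stated total of 246 reproduces: a two-sided t-test at 5% with 80% power and d = 0.36 needs 122.09 per arm, rounded up to 123, or 246 in total. That calculation concerns the primary outcome and is used here only for n. Both q and δ are assumptions, because the article gives neither.

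With no true effect and 123 rated patients per arm, the standard error in SD units is √(2/123) = 0.1275. The false-positive rate is Φ(b/0.1275 − 1.96) + Φ(−b/0.1275 − 1.96).

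| Share q rated by clinicians | δ = 0 | δ = 0.1 | δ = 0.2 | δ = 0.3 |
|---|---|---|---|---|
| 0.25 | 5% | 5.4% | 6.8% | 9.0% |
| 0.50 | 5% | 6.8% | 12.3% | 21.7% |
| 1.00 | 5% | 12.3% | 34.8% | 65.3% |

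For example, q = 0.5 and δ = 0.3 give b = 0.15 and b/0.1275 = 1.18, hence 21.7%. This is a plain two-group comparison at one visit, not the planned mixed model. The table shows that the consequence runs from nothing to substantial depending on two unknowns. It does not estimate the bias in this trial.

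**The case against.** The strongest reply is that the article never says the raters are unblinded. It writes of treating clinicians in the Sample section but only of clinicians for the GAF, it allows trained study personnel as well, and clinician input stands openly beside the blinding statement in Methods against bias. On this view the sections are ambiguous rather than contradictory. If the GAF is rated only at t0 and t3, no rating is exposed at all. The outcome is also exploratory, and a clinician who sees the patient daily may judge functioning better than an interviewer does.

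Much of this stands. It limits the point to a risk at t1 and t2, conditional on the schedule, and it makes the point minor. It does not remove the inconsistency: one section promises blind assessors outside treatment, and another sets a rater rule that can be followed to the letter without meeting that promise.

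A reader might go further and infer three things that the article does not support.

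- **That the GAF result is biased.** Neither the clinicians' knowledge of allocation nor any leniency is documented, and the direction of a shift is not known either.
- **That a switch to study personnel at t3 makes the group-by-time result unreadable as a treatment effect.** A rater change common to both arms cancels, as step 4 of the working shows, and nothing suggests that rater type differs by arm.
- **That the bias rivals the effect the trial is planned on.** The planned d belongs to the primary outcome, days of substance use, and any GAF bias set beside it would be one assumption divided by another.

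**Conclusion.** The point holds as an inconsistency of minor severity. As written, the GAF rule permits rating by clinicians who need not be blind or outside the treating team, contrary to the safeguard stated in Methods against bias. Ratings made after randomization and during treatment are therefore open to detection bias of unknown size. This rests on two conditions that the available text does not settle: that the GAF is scheduled at t1 or t2, and that some of those ratings are made by clinicians who know the allocation.

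The t0 rating, the t3 rating as assigned under Procedure, the primary outcome with its confirmatory t3 contrast, and the sample size are unaffected.

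**What to change.** Amend General level of functioning so that every post-randomization GAF rating analysed as the outcome is made only by the blinded study personnel described in Methods against bias. A GAF recorded by a clinician can be kept as descriptive information and left out of the outcome analysis. Because the article reports that recruitment is under way, record the rater type (clinician or blinded study personnel) for ratings already made, so that the share of clinician ratings is known when the GAF is reported.

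The cost is one sentence, one recorded item, and a rating added to interviews that these personnel already conduct. The article gives no staffing figures, so the extra time cannot be quantified. The small downside is that an interviewer knows the patient less well than the clinician does.

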#### Number of disability days

Within our clinical standard procedure, we assess the number of days within the past 30 days on which participants felt unfit to attend school or pursue their normal daily activities.

#### Medication

As a further clinical standard procedure, we will document any medication use from 30 days before treatment begin to the *t*_3_ assessment.

#### Sexual risks

As a further indicator of previous trauma and sexual health behavior, we ask participants to indicate previous incidents of sexual harassment and sexual assault. These items have been used successfully in previous research [53, 54].

#### Health-related quality of life

KIDSCREEN-10 is a 10-item validated and reliable self-report tool for the assessment of subjective health and well-being (e.g., “Do you feel fit and well?”) in children and young people aged up to 18 [55]. Cronbach’s alpha for KIDSCREEN-10 is .82.

#### Satisfaction with intervention group

Patients will be asked to provide self-reports of how they viewed the mindfulness-based group intervention through the *Gruppentherapiestundenbogen* (GTS-P) [56], an eight-item German-language tool (e.g., “The atmosphere within the group was good today”), which has good validity and internal consistency (Cronbach’s alpha between .79 and .91).

#### Participant’s mindfulness

Due to the centrality of mindfulness in our study, mindfulness will be measured through two self-report assessment tools: (1) the Mindful Attention Awareness Scale for Adolescents (MAAS-A) [57], which was chosen by the larger consortium into which our study is embedded, and (2) the Mindfulness Thinking and Action Scale for Adolescents (MTASA) [58], which has proved to be valuable in previous research on the intervention [44]. MAAS-A is a 14-item scale that mostly targets the absence of mindful experiences (e.g., “I snack without being aware that I’m eating”). It has shown good internal consistency (Cronbach’s alpha from .82 to .84) and validity in both normative and psychiatric samples and has been proved to be sensitive to change in mindfulness-based intervention research. MTASA is a 32-item scale and consists of four subscales that focus on different aspects of mindfulness: healthy self-regulation, active attention, awareness and observation, and accepting experiences. MTASA has been validated and both the total scale (Cronbach’s alpha = .86) and the subscales (Cronbach’s alpha between .63 and .85) have acceptable internal consistency.

